### Sample size

#### Aim 1 - within group analysis sample size

A sample size of 21 achieves 90% power to detect a mean of paired differences of 3.0 with a significance level of 0.05 using a two-sided paired t-test. A sample size of 34 achieves >90% power to detect a difference of 3.0 with a significance level of 0.05 using a two-sided Wilcoxon Signed-Rank test. Assuming at least 20% of the sample changes between baseline and follow-up a sample size of 115 pairs achieves 80% power to detect an odds ratio of 3.0 using a two-sided McNemar’s test with a significance level of 0.05. The odds ratio is equivalent to a difference between two paired proportions of 0.10.

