#### Recruitment and screening of the evaluation cohort

We propose to recruit 50 participants per development in the evaluation cohort. Eligibility criteria include being able to speak English or Spanish, being 18 years old or older, being a public housing resident from one of our study sites, not planning to move within the next 2 years, having access to a phone, not currently participating in another physical activity study, being able to walk independently without regular need for special equipment (wheelchair, scooter, or walker), ability to provide informed consent, and willingness to complete the accelerometer-based device measurement. By design, the entire cohort will be low-income.

Recruitment will take place at the developments, using common sampling rules and a direct household door-knocking approach [39–41]. Trained Research Assistants will approach units based on an assigned list and will attempt to identify an eligible resident using a brief script. The survey steps will be as follows: approach the unit, attempt to identify a resident, describe the study, determine eligibility, collect informed consent documents, collect the survey measurements, explain the physical activity device, and remind the residents of follow-up visits. Data collection documents for screening, documenting informed consent, and baseline, 12- and 24-month assessments are stored in REDCap [42].

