##### Within group analysis

Preliminary analysis will examine within group differences in each of the study groups from baseline to the end of the intervention at 2 years. Minutes of moderate or greater intensity activity per week will be examined using paired t-test if the distribution is approximately normal or the nonparametric Wilcoxon signed-rank test if normality cannot be assumed. McNemar’s chi-squared test will be used for a paired analysis of meeting recommended physical activity level (binary outcome) pre and post intervention.

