#### Aim 1 - between group analysis sample size

We power the multivariable analysis based on test for two means in a 2-level hierarchal design with level 2 randomization. Sample sizes of 96 subjects in each group, which were obtained by sampling 3 clusters with an average of 32 subjects per cluster, achieve >90% power to detect a difference between the group means of at least 5 minutes (or 5 percent difference in meeting recommended levels). A test based on a mixed-model analysis at a significance level of 0.05.

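### The within-group McNemar power is misstated: 115 pairs give about 67% two-sided power, not 80%, and the preliminary paired tests ignore clustering by development

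*Protocol article*

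**What the plan says.** The protocol article, under Aim 1 - within group analysis sample size, gives a complete McNemar specification:

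- Share of changers: "Assuming at least 20% of the sample changes between baseline and follow-up".
- Size, power, effect and sidedness: "a sample size of 115 pairs achieves 80% power to detect an odds ratio of 3.0 using a two-sided" McNemar test, at a significance level of 0.05.
- The same effect on the difference scale: "The odds ratio is equivalent to a difference between two paired proportions of 0.10".

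The Within group analysis section plans these tests separately in each study group and labels them preliminary. Weekly minutes of activity "will be examined using paired t-test if the distribution is approximately normal", otherwise by the Wilcoxon signed-rank test. Meeting the guideline is compared before and after by McNemar's test. Neither section mentions clustering or an ICC.

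Group sizes appear in several places:

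- Recruitment: "We propose to recruit 50 participants per development in the evaluation cohort", with three developments per group (Recruiting public housing developments), so 150 per group.
- Between-group power: "Sample sizes of 96 subjects in each group, which were obtained by sampling 3 clusters with an average of 32 subjects per cluster".
- Moderation: 40 per development (RCP method) and 41 (LMS method), so 120 and 123 per group.

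**The concern.** There are two separate matters.

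First, the stated power does not follow from the stated inputs. Meeting the guideline is one of the two outcomes that the Between group analysis section calls primary, and this sentence is the only power statement for its pre-post test. A reader would take 115 pairs per group as enough for 80% power.

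Second, the paired tests assume that residents' changes are independent, yet each group consists of only three developments. If residents of one development tend to change together, the within-group p-values are too small. A pre-post change would then be called significant too often in any arm, control included. The protocol uses multilevel models for the between-group and interaction questions, so it recognises clustering there and omits it here.

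**Working it through.** **Inputs, all from the within-group sample size section.** Discordant proportion pd = 0.20; odds ratio 3.0; difference d = 0.10; two-sided alpha 0.05; n = 115; stated power 80%.

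**Consistency.** With pd = 0.20 and odds ratio 3.0, the discordant cells are 0.15 and 0.05, so d = 0.15 − 0.05 = 0.10. The inputs agree with each other and no outside assumption is needed.

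**Power at 115 pairs.** Standard unconditional formula: z = (d√n − 1.96√pd) / √(pd − d²).

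- d√n = 0.10 × √115 = 1.0724
- 1.96 × √0.20 = 0.8765
- √(0.20 − 0.01) = 0.4359
- z = (1.0724 − 0.8765) / 0.4359 = 0.449, so power is 67.3%. The stated 80% is not reproduced.

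**Pairs for 80%.** n = (1.96√pd + 0.8416√(pd − d²))² / d² = (0.8765 + 0.3669)² / 0.01 = 154.6, so 155.

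**Does the version of the test matter?**

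| Version (two-sided 0.05) | Power at 115 | Pairs for 80% |
|---|---|---|
| Standard formula | 67.3% | 155 |
| Wald | 69.2% | 150 |
| Simple | 66.9% | 157 |
| Conditional | 69.4% | 145 |
| Enumeration, uncorrected | 70.5% | 145 |
| Enumeration, mid-p | 67.8% | 152 |
| Enumeration, exact | 61.2% | 168 |
| Enumeration, continuity-corrected | 60.4% | 169 |

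No two-sided version comes near 80%.

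**Where 115 may come from.** One-sided at 0.05, the standard formula gives 78.0% at 115 pairs, Wald 79.3%, conditional 80.8% and uncorrected enumeration 79.4%. The simple formula gives 77.4%, and the exact and corrected versions about 74%. A one-sided calculation labelled two-sided therefore fits. So does a two-sided calculation with pd = 0.15 and d = 0.10 (n = 115.3), but its cells are 0.125 and 0.025, an odds ratio of 5, which contradicts both the 20% and the 3.0. The source cannot be settled from the document.

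**Power at the protocol's other sizes** (standard formula, two-sided, before clustering):

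- 96 (between-group calculation): 59%
- 120 and 123 (moderation calculations): 69% and 70%
- 150 (recruited, no dropout): 79%

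**Clustering.** No ICC is stated, so the ICC values for change below are assumptions. The design effect is DE = 1 + (m − 1) × ICC, and the approximate type I error of a nominal 5% test is 2 × [1 − Φ(1.96/√DE)].

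| Assumed ICC | DE, m = 32 | Type I error | DE, m = 50 | Type I error |
|---|---|---|---|---|
| 0.01 | 1.31 | about 9% | 1.49 | about 11% |
| 0.02 | 1.62 | about 12% | 1.98 | about 16% |
| 0.05 | 2.55 | about 22% | 3.45 | about 29% |

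Simulating the paired t-test on 3 × 32 people (20,000 replicates) gave 8.9%, 12.3% and 22.2%, which agrees with the approximation.

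**The case against.** The strongest reply on the arithmetic is that the protocol says at least 20%, so more people may change. This does not rescue the figure. With the odds ratio held at 3.0, 115 pairs reach 80% only at about 27% discordant (n = 113.9), where the difference is 0.135 and not 0.10. If the difference is held at 0.10 instead, more changers mean more pairs are needed.

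The reply on consequence stands in large part. The 115 does not set enrolment: 150 are recruited per group, and full retention leaves power about one point short of 80% before clustering. The within-group tests are labelled preliminary, and Hypothesis 1 is a comparison with control. A reader might infer that the error undermines the primary analysis or supports an effectiveness claim from within-arm change. The protocol rests no hypothesis on these tests.

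A reader might also infer that only 96 pairs per group are planned, so that real power is 59%. The document does not say so. The 96 is the size used in the between-group calculation and is nowhere called the expected or evaluable number. No retention rate is given. As retention, 32 of 50 would be 64%, while the moderation calculations use 40 and 41 per development.

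On clustering, one could argue that a within-arm test describes only the three developments in that arm, for which development effects are fixed. The protocol does not limit the inference in that way. What stands is that the size of the inflation is unknown without an ICC, and there is none if the ICC of change is zero.

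**Conclusion.** The power statement is wrong as written, and this rests only on the protocol's own inputs: about 67% at 115 pairs instead of 80%, with about 155 pairs needed. The choice of test moves these to 60% to 70% and 145 to 169, and does not change the conclusion. At the planned 150 per group the shortfall is about one point with no dropout; it is about ten points at 120 to 123.

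That the preliminary paired tests carry no allowance for clustering is also established from the text. The type I error figures (about 9% to 22% at 32 per development, 11% to 29% at 50) are illustrations under assumed ICCs of 0.01 to 0.05.

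This should be fixed but is not critical: the analyses are preliminary and the primary between-group inference does not depend on them.

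**What to change.** Restate the McNemar sentence along these lines: about 67% power at 115 pairs and about 79% at 150 pairs, with about 155 pairs needed for 80%, before any allowance for clustering. If a one-sided test was meant, say so and justify it.

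Replace the unclustered paired tests with within-arm change estimated from the multilevel model across all 12 developments. Use a random development effect and small-sample degrees of freedom, and report the estimate with a 95% confidence interval.

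The cost is rewording and recalculation, a less favourable stated power, and wider within-arm intervals. No extra participants are needed.

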#### Aim 1 - between group analysis sample size

We power the multivariable analysis based on test for two means in a 2-level hierarchal design with level 2 randomization. Sample sizes of 96 subjects in each group, which were obtained by sampling 3 clusters with an average of 32 subjects per cluster, achieve >90% power to detect a difference between the group means of at least 5 minutes (or 5 percent difference in meeting recommended levels). A test based on a mixed-model analysis at a significance level of 0.05.

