## Methods/design

### Participants

The study setting is family-designated public housing developments in the City of Boston managed by the Boston Housing Authority (*N=*16) and other housing developments serving low-income populations managed by a private management company (*N=*26). Boston Housing Authority developments provide housing for nearly 13,000 low-income people who identify as white (9%), Black (33%), Hispanic (51%), or other (7%). Approximately two-thirds of adult residents are women. About 90% of residents speak English and/or Spanish. Prevalence of obesity and related health conditions are higher among individuals living in Boston's public housing developments compared to other city residents [37]. Approximately 62% of Boston public housing residents report insufficient physical activity [37] and, qualitatively, report environmental structural barriers to physical activity [38].

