##### Between group analysis

The between group hypothesis is tested in three separate bivariate analyses comparing each intervention group to the control group in two primary outcomes based on the cluster-randomized design. We examine change in each primary outcome pre-intervention to post-intervention: 1) the number of minutes of moderate or greater intensity physical activity per week (continuous); and 2) meeting the recommended guidelines of >150 minutes of moderate or greater intensity physical activity per week (dichotomous at individual level, proportion at group level). In addition, we will examine this hypothesis controlling for potential confounding factors and any variables that violate the randomization assumption using multilevel multivariable linear (continuous outcomes) and logistic (binary outcomes) regression models.

Hypothesis 2: Participants living in developments receiving the combined intervention (E+I) will demonstrate even greater increases in the number of minutes of moderate intensity physical activity per week (individual level) and the proportion meeting the recommended physical activity guidelines (development level) from baseline to 24-month follow-up, compared to either intervention delivered singly.

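### Power above 90% for a 5-point difference in meeting the activity guideline cannot be reached with 96 residents per arm, at any baseline rate or ICC

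*Protocol article*

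**What the plan says.** Under Sample size, Aim 1 - between group analysis sample size, the calculation is described as a "test for two means in a 2-level hierarchal design with level 2 randomization". The size is given as "Sample sizes of 96 subjects in each group", "obtained by sampling 3 clusters with an average of 32 subjects per cluster". These numbers are said to "achieve >90% power to detect a difference between the group means of at least 5 minutes (or 5 percent difference in meeting recommended levels"). The section closes with "A test based on a mixed-model analysis at a significance level of 0.05". It gives no baseline proportion, SD, ICC or sidedness.

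Under Analysis plan, Between group analysis, each intervention arm is compared with control on change in two primary outcomes. The second is "meeting the recommended guidelines of >150 minutes of moderate or greater intensity physical activity per week (dichotomous at individual level, proportion at group level").

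The only rate in the document that bears on guideline attainment is under Participants: "Approximately 62% of Boston public housing residents report insufficient physical activity".

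Under Aim 1 - within group analysis sample size, 115 pairs are said to give 80% power for a paired difference of 0.10 in the binary outcome, assuming that at least 20% change status.

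**The concern.** The sentence treats a 5-minute difference in means and a 5-point difference in proportions as interchangeable targets with the same power. They are not. The variance of a yes/no outcome is fixed by its rate, so its power can be bounded without knowing any SD. A 5-point difference is small for 96 per arm even if residents were independent, and here they are clustered in three developments per arm.

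The document also sits badly with itself. For the same outcome it claims 80% power for a 10-point paired difference with 115 pairs. It then claims more power for half the difference, with fewer people per group and a comparison between separate clustered arms.

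At stake is how the guideline result is read. The Between group analysis section calls this outcome primary, and a stated power above 90% tells readers that a 5-point effect would very probably have been detected.

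**Working it through.** **Inputs**
- 96 per arm, 3 developments of 32; alpha 0.05, sidedness not stated, so both are tried (sample size section).
- Difference 0.05, read as percentage points.
- Baseline rate: none is given for this calculation, so every lower rate from 0% to 95% is scanned. The value 38% = 100% − 62% is an assumption.
- ICC: none is given. It is set to 0 first, the most favourable case, then ranged from 0 to 0.05 as an assumption.

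**1. Trying to reproduce the stated power.** For two means with 96 per arm and ICC 0, 90% power two-sided needs

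SD = 0.05 / [(1.960 + 1.282) × √(2/96)] = 0.05 / (3.242 × 0.1443) = 0.107.

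The average variance of a yes/no outcome at rates p and p + 0.05 is [p(1−p) + (p+0.05)(0.95−p)]/2. Its smallest value, at p = 0 (or 0.95), is 0.0475/2 = 0.02375, so SD = 0.154. That exceeds 0.107, and the stated figure is not reproduced.

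**2. 38% v 43%, ICC 0.** SE = √[(0.38×0.62 + 0.43×0.57)/96] = √(0.4807/96) = 0.0708, and 0.05/0.0708 = 0.707.
- Two-sided power = Φ(0.707 − 1.960) = Φ(−1.253) = 10.5%. Exact enumeration gives 10.6% to 10.9%. One-sided it is about 17%.
- With 150 per arm: SE = √(0.4807/150) = 0.0566, and Φ(0.883 − 1.960) = 14.1%. Exact enumeration gives 14.7%.

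**3. All baseline rates, 96 per arm, ICC 0** (two-sided, normal approximation)

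| Lower rate | Power |
|---|---|
| 0% | 60.3% |
| 1% | 47.0% |
| 5% | 25.9% |
| 10% | 18.0% |
| 20% | 12.9% |
| 30% | 11.1% |
| 38% | 10.5% |
| 47.5% | 10.2% |
| 62% | 10.8% |
| 80% | 14.7% |
| 95% | 60.3% |

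The normal approximation is poor at the extremes, so the best case was also done exactly. At 0% v 5% the control arm has no events. The two-sided pooled z-test rejects once the other arm has 4 events (z = 2.02), and P(≥4 | 96, 0.05) = 71.3%. One-sided, 3 events suffice (z = 1.75), and P(≥3 | 96, 0.05) = 86.4%. Both are below 90%.

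**4. Change from baseline.** The plan analyses change, so this was tried too. If 20% of each arm changes status, SE = √[(0.20 + 0.1975)/96] = 0.0643, and Φ(0.777 − 1.960) = 11.8%. If no control resident changes and 5% of intervention residents gain with none losing, the variance is 0.0475 in one arm only, which is again the 0% v 5% case (61% by the unpooled formula). Baseline adjustment at 38% gives 12.6% for a correlation of 0.5 and 36.7% for 0.9.

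**5. Clustering.** With design effect 1 + 31 × ICC, power for 38% v 43% with 96 per arm is:

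| ICC | Normal | t, 4 df |
|---|---|---|
| 0 | 10.5% | 8.6% |
| 0.01 | 9.0% | 7.7% |
| 0.02 | 8.0% | 7.2% |
| 0.05 | 6.5% | 6.4% |

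The 4 df are 3 + 3 − 2 developments in one pairwise comparison.

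**6. What 96 per arm could detect from 38% with 90% power (illustration).**
- Normal test, ICC 0: power is 89.6% at 61% and 92.0% at 62%, so about 23 points.
- t(4): the critical value is 2.776, and 90% power needs difference/SE of about 4.40. At ICC 0, 38% v 68.2%: SE = √[(0.2356 + 0.2169)/96] = 0.0687, and 0.302/0.0687 = 4.40, so about 30 points. At ICC 0.05 (design effect 2.55), 38% v 82.3%: SE = √[(0.2356 + 0.1457) × 2.55/96] = 0.1006, and 0.443/0.1006 = 4.40, so about 44 points.

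**The case against.** **A test of means, or of group-level proportions.** A proportion averaged over three clusters of 32 still carries the binomial variance of its members. Step 1 is already on the scale of means, and clustering only adds to it.

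**Percent may mean relative.** A relative 5% is a smaller absolute gap at any rate, so power would be lower still.

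**This is a condensed article.** The SD and ICC may well stand in the full protocol, and their absence is no fault here. The objection does not help the binary claim, because no ICC of 0 or more rescues it.

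**38% is not the cohort's rate.** This stands. The 62% is self-reported by residents in general, whereas the outcome is device-measured in independently walking volunteers. A reader might infer that power is 11% whatever the baseline. It is not: 11% belongs to 38%, ICC 0 and a two-sided test. Only the failure to reach 90% is general.

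**The cohort is planned at 150 per arm.** The bound is for the 96 in the stated sentence. At 150 per arm, ICC 0 and 0% v 5%, the exact two-sided figure does pass 90% (94.5%), but only in that degenerate case. At 38% it is about 14%.

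**Guideline attainment may not be primary.** The abstract and the Primary outcome measurement section name activity minutes alone. Only Between group analysis lists two primary outcomes. This tempers the consequence but leaves the stated power wrong.

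A reader might also infer that the 5-minute claim is false. The document gives no SD or ICC against which to test it, so that inference is not supported.

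**Conclusion.** The claim of more than 90% power for a 5-point difference in guideline attainment is wrong as written. With 96 per arm it fails at every baseline rate, at every ICC of 0 or more, and one-sided or two-sided; the ceiling is 60% (normal approximation), 71% (exact two-sided) or 86% (exact one-sided), all in degenerate cases. Under the assumed 38% baseline, ICC 0 and two-sided 0.05, power is about 11%. No other section corrects the figure, and the within-group statement of 80% power for a 0.10 difference with 115 pairs (taken here as stated) is hard to square with it.

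The size of the shortfall depends on the assumed baseline and ICC; the conclusion that 90% is not reached does not. It would go too far to infer that the guideline test must be dropped or enrolment enlarged. The error is in a stated power, and correcting that statement is enough.

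**What to change.** In Aim 1 - between group analysis sample size, delete the parenthesis on guideline attainment. Alternatively, replace it with the difference in the proportion that the fixed sample size can detect, computed from the sponsor's own baseline rate, ICC and reference distribution, with those three inputs stated. The figures in step 6 (about 23 points at ICC 0 with a normal test; about 30 to 44 points with t(4) over ICC 0 to 0.05) show the order of magnitude. They rest on an assumed 38% and an assumed ICC range and should not be copied in as the trial's own. Do not describe the guideline outcome elsewhere as powered above 90%.

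The cost is one sentence and, for the second option, a short calculation. Enrolment, design and the planned tests are unchanged. The price is a less favourable power statement for that outcome.

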#### Aim 2 – mediation

The test of mediation effect is based on Sobel’s test. A sample size of 395 achieves 90% power to detect a mediation effect of at least 0.04 as measured by the product of two regression coefficients 0.20 (primary predictor) and 0.20 (mediator) when the significance level is 0.05.

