#### Aim 2 – moderation

##### RCP method

A total sample size of 480 observations, were obtained by sampling 3 level-2 units (PHD) in the control group, 3 level-2 units (PHD) in I only group, 3 level-2 units (PHD) in the E only group, and 3 level-2 units (PHD) in the E+I group. Finally, 40 level-1 units (individuals with repeated measurements) were obtained from each level-2 unit (PHD). This sample achieves >90% power to detect a three-way interaction among the subject-specific slopes of at least 3.0. A test based on a mixed-model analysis assuming random slopes will be used. This test will be conducted at a significance level of 0.05.

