##### LMS method

A total sample size of 492 level-1 units (individuals), which were obtained by sampling 3 level-2 units (PHD) in the control group, 3 level-2 units (PHD) in I only group, 3 level-2 units (PHD) in the E only group, and 3 level-2 units (PHD) in the E+I group, with an average of 41 level-1 units (individuals) per level-2 unit (PHD), achieve >85% power to detect an interaction difference among the group means of at least 3.75. A test based on a mixed-model regression analysis at a significance level of 0.05.

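### The 90% mediation power at 395 people holds only if residents are independent, although the intervention is assigned to 12 developments

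*Protocol article*

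**What the plan says.** The protocol article, under Sample size, Aim 2 – mediation, says: "The test of mediation effect is based on Sobel’s test". It continues: "A sample size of 395 achieves 90% power to detect a mediation effect of at least 0.04". The effect of 0.04 is the product of a coefficient of 0.20 for the primary predictor and one of 0.20 for the mediator, "when the significance level is 0.05". This paragraph gives no number of developments, no number of residents per development and no allowance for clustering.

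The paragraphs around it do set out the cluster structure. The between-group calculation for Aim 1 is built from "3 clusters with an average of 32 subjects per cluster", and both moderation calculations are described as three developments per arm with a stated number of residents in each.

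Design of the Community Walks study makes the housing development the unit of randomisation, with 12 developments in four arms of three. The Statistical analysis section under Aim 2: mediation/moderation plans multilevel structural equation models for mediation and itself remarks that clusters are few.

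**The concern.** A mediated effect is the product of two paths: intervention to mediator (a) and mediator to outcome (b). In this trial every resident of a development has the same intervention status, so path a is a comparison between developments. If residents of one development resemble each other on the mediators (motivation, self-efficacy, perceived walkability, support from the community health workers), 395 residents carry less information about path a than 395 independent people would.

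A power figure that ignores this describes a different design from the one randomised and a different model from the one planned. At stake is how the mediation results can be read. With a printed 90%, a null result looks like fairly strong evidence against a mediated effect of the stated size. With power nearer 50% to 80%, it does not.

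**Working it through.** **Inputs.** From Sample size, Aim 2 – mediation: a = 0.20, b = 0.20, N = 395, significance level 0.05, Sobel's test. From the design section: 12 developments. Assumed here: a two-sided test, unit variances, and ICCs of 0.01, 0.02 and 0.05 for the mediator. The article states none of these.

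**Step 1: reproduce the plan's figure.** The Sobel statistic is z = ab / sqrt(a² × SE_b² + b² × SE_a²). With independent residents, SE_a and SE_b are each about 1/sqrt(395) = 0.0503. Simulating the two-sided test under these inputs gives:

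- N = 395: about 90% power
- N = 384: about 88.5% to 89%

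The stated 90% is therefore the independent-person answer.

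A shortcut gives a different answer and should not be used. Putting the true values into the formula gives z = 0.04 / (0.20 × sqrt(2/395)) = 2.81, and Phi(2.81 − 1.96) is about 80%. That step assumes the Sobel statistic has a standard deviation of 1. At these inputs its simulated standard deviation is about 0.55, so the shortcut understates power. The protocol's arithmetic is right for the model it used.

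**Step 2: put clustering on the intervention path only.** Residents per development: 395/12 = 32.9. Design effect: DE = 1 + (32.9 − 1) × ICC. Then SE_a = 0.0503 × sqrt(DE), with SE_b unchanged.

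| Assumed ICC | DE | SE_a | Simulated power at N = 395 |
|---|---|---|---|
| 0 (as in the protocol) | 1.00 | 0.0503 | about 90% |
| 0.01 | 1.32 | 0.0578 | about 83% |
| 0.02 | 1.64 | 0.0644 | about 74% |
| 0.05 | 2.60 | 0.0811 | about 53% |

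**Step 3: direction of what is left out.** These figures use the normal critical value of 1.96. With 12 developments, the reference distribution for path a has few degrees of freedom and a larger critical value, so true power is somewhat lower. Leaving SE_b uninflated is also the lenient choice.

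**The case against.** **The inputs may be in the full protocol.** The article condenses a longer document, and an unstated ICC is not in itself a fault. That is fair, and the missing ICC is not the point here. The printed 90% at 395 is matched with no clustering at all, so the calculation contradicts the design whatever ICC is recorded elsewhere.

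**More than 395 people may be available.** "We propose to recruit 50 participants per development in the evaluation cohort" gives 12 × 50 = 600. This carries some weight. If all 600 were analysable and the ICC were 0.01, DE = 1 + 49 × 0.01 = 1.49 and SE_a = sqrt(1.49/600) = 0.0498. That is no larger than the 0.0503 behind the protocol's figure, so 90% would be met before the correction for 12 clusters. At an ICC of 0.05, DE = 3.45 and SE_a = sqrt(3.45/600) = 0.0758, only slightly better than the 0.0811 at 395. Extra residents help only if the ICC is small, and the printed statement is about 395.

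**Mediation is a secondary aim, and the protocol acknowledges the small number of clusters.** Both are true, and they limit the importance of the point. The acknowledgement appears in the analysis section and is not carried into the power statement. Nothing in the article says that a null mediation result will be read as absence of effect.

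**Two stronger readings that the article does not support.**

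- A reader might infer that 32, 40 and 41 residents per development, used in the Aim 1 and the two moderation calculations, contradict each other. Each is given as a number sufficient for its own test. None is called evaluable or expected at follow-up. The largest total, 12 × 41 = 492, fits within 600 if 82% are analysable. That 395 exceeds 12 × 32 = 384 is worth only about 1 to 1.5 points of power.
- A reader might infer that the moderation power claims are impossible beside the 5-minute pairwise difference. That means treating a three-way interaction of subject-specific slopes as a two-by-two contrast of means, and treating back-calculated upper limits on the standard deviation as if the protocol had assumed them.

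**Conclusion.** The point holds for the mediation power statement alone. The 90% at 395 is correct for independent people and is not what a trial of 12 randomised developments provides at that number. The shortfall at 395 is about 7 points at an ICC of 0.01, 16 at 0.02 and 37 at 0.05, before any correction for few clusters. The size rests on those assumed ICCs, on unit variances and a two-sided test, and on inflating only the intervention-to-mediator path. The direction does not depend on the particular ICC: any positive clustering of the mediator lowers power at 395. The point leaves the Aim 1 and moderation sample sizes untouched.

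**What to change.** Recompute the mediation power with the intervention path at development level. State the ICC used for the mediator and the number per development expected to be analysable, and use degrees of freedom suited to 12 clusters. Replace the 90% in Sample size, Aim 2 – mediation with the result. If it is well below 90%, label the mediation analysis exploratory and report indirect effects with confidence intervals.

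The cost is a recalculation, a change of wording and a less favourable stated power. No extra participants are needed.
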